### Safety variables

#### Adverse events

- Adverse events recorded during the follow up
- Serious adverse events
- Deaths

#### Laboratory safety variables

Haematological parameters: haemoglobin, platelets, leukocytes, neutrophils

Biochemical parameters:, blood creatinine, total bilirubin, ALT

#### Vital signs

- Axillary temperature at each time of measurement

## Analysis populations

### Efficacy populations

The following populations will be defined for the analysis,:

- Intent to treat (ITT) population: all included patients known to have received at least one dose of treatment (excluding patients with double rejection or vomiting at the first intake).
- Per protocol (PP) population all ITT population patients that completed the study treatment in accordance with the study protocol and completed all specified assessments without major violation

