| EVALUATION CRITERIA | - PCR corrected and uncorrected clinical and parasitological cure rate at D28 and D42 ( WHO classification) - Fever and parasitological clearance (for the 1st attack) by measuring the axillary temperature and monitoring parasitemia - Proportion of afebrile patients at D3 and proportion of patients without parasites at D3 (for following attacks) - Clinical efficacy : evolution of baseline symptoms (all clinical symptoms will be graded) - Compliance based on number of residual tablets in blisters - Treatment incidence density during the 2 years of follow up (comparison of the number of malaria attacks between the two arms during the 2 years) - Mean delay between 2 attacks during the 2 years of follow up - Clinical tolerability ( incidence and intensity of recorded AE ) - Biological tolerability (Hb, Bilirubin, ALAT, Creatinine, Leukocytes, Neutrophils, and Platelets count) |
| RESCUE TREATMENT | Because PCR will not be available in real time:  Any failure before D14, will be considered as a recrudescence and will receive rescue treatment  Failure at D14 or later will be considered as reinfection; and the same ACT treatment will be repeated |
| ASSESSMENT SCHEDULE | Refer to flowchart |
| STATISTICAL CONSIDERATIONS | **Number of patients:**  With a non-inferiority margin () chosen at 5 %, =5%, and  =20%, and the hypothesis of 97% of success rate with Coartem®, 174 patients are requested; taking account of 15% of lost follow-up 200 patients are needed per treatment group.  **Statistical generalities**  All statistical analyses will be performed on SAS software (version 8.2 for PC).  All statistical tests will be bilateral and performed at a 5% significance level excepted for the non-inferiority analysis (unilateral confidence interval)  **Efficacy Analysis**  The non-inferiority of PCR adjusted adequate clinical and parasitological response at D28 (WHO protocol in vivo D28 2003) of Coarsucam® (artesunate plus amodiaquine) versus Coartem® (artemether plus lumefantrine), based on the first malaria attack of each patient will be studied using the 95% one-sided confidence interval on ITT and Per Protocol populations. |
| DURATION OF STUDY PERIOD | 2 years  Each attack will be actively followed for 42 days |

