## Concomitant treatment

### Prohibited medication

Any antimalarials or antibiotic with antimalarial activity (erythromycin or other macrolides, co-trimoxazole or other sulphonamides, any tetracycline including doxycycline, and quinolones, clindamycin…) is not authorised during the study follow up of 42 days. Intake of these drugs leads to withdrawal of the patient from the ongoing active follow up. However, the patient will be kept in the passive follow up and when presenting with another clinical malaria episode fulfilling the inclusion/exclusion criteria, another active follow up can be started. There are no disallowed concomitant therapies during the passive follow up.

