### Management of treatment failures

Patients treated for uncomplicated malaria that are classified as failures (within 14 days of treatment) will be treated with quinine (10 mg/kg TID x 7d). In the unlikely event that a patient fails to have an adequate clinical response to quinine (either as first-line therapy for complicated disease or second-line therapy), treatment will be repeated with quinine (3 days) and clindamycin (5 mg/kg QID for 7 days). In this case, a failure CRF will be completed and patient will be followed-up until D42 from the initial enrolment Safety medication will be recorded in the failure case report form.

In experience of the site, failure to respond to quinine therapy is generally an indication of non-compliance. In the very unlikely event that a patient fails to have an adequate clinical response to quinine plus clindamycin therapy or if they develop severe or complicated malaria, they will be referred to Nagongera Health Centre IV or Tororo Hospital for further evaluation.

Treatment failures occurring on D14 or later have to be considering as reinfections and have to be treated with the same ACT allocated by the randomisation.

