## Treatment discontinuation with investigational product(s)

### List of criteria for treatment discontinuation

The objective criteria for discontinuing the study treatment and resorting to a safety treatment are as follows:

- Withdrawal of informed consent: The parents/guardians may withdraw the patient from treatment with Investigational Product if they decide to do so, at any time and irrespective of the reason, or this may be the Investigator’s decision
- onset of one or more danger signs/or signs of complicated malaria, according to the WHO definition (cf. Appendix 4),
- parenteral treatment becomes necessary,
- onset of an adverse event justifying treatment discontinuation
- repeated vomiting/rejection

If the patient’s condition progresses in an unsatisfactory manner, he/she will be directed to the centre’s referring facilities.

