## Determination of sample size

The main analysis will be based on the non–inferiority testing of Coarsucam® (fixed dose combination of artesunate plus amodiaquine) versus Coartem® (artemether plus lumefantrine) for the first attack (supervised intakes).

The acceptable non-inferiority margin () in proportion of success between Coarsucam® and Coartem®, has been chosen at 5 %.

The test of non inferiority between Coarsucam® group and Coartem® group will be based on the unilateral confidence interval method with =5%, and  =20%,

According to Mutabingwa (7) failure rate at D28 is about 2.7% for Coartem ® (97% of successes) in East Africa (Tanzania).

With these hypotheses (computed with Nquery advisor Software, process PTE1a-1) 174 patients are needed by group of treatment.

Finally 200 patients will be included in each group in order to take account of 15% of prematurely withdrawal.

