### Analysis of efficacy variables

The efficacy data analysis will be performed on the ITT population and on the Per Protocol population.

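### The per-protocol definition requires completed treatment and assessments with no clause keeping classified failures, so some failures leave the set because they failed, tilting that analysis toward non-inferiority

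*Protocol*

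**What the plan says.** Section 14.4.1 defines ITT as "all included patients known to have received at least one dose of treatment", less children with double vomiting or rejection at the first intake. It defines PP as "all ITT population patients that completed the study treatment in accordance with the study protocol and completed all specified assessments without major violation". No sentence covers children who meet a failure definition before the course or the visit schedule ends.

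Both sets carry the primary analysis. The Synopsis says that non-inferiority "will be studied using the 95% one-sided confidence interval on ITT and Per Protocol populations", and section 14.5.3 says "The efficacy data analysis will be performed on the ITT population and on the Per Protocol population". Neither set is named as the leading one, and no rule covers disagreement between them.

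Four other places bear on who can complete:

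- Section 12.1.1 lists among the reasons to stop study drug the "onset of one or more danger signs/or signs of complicated malaria". Appendix 1 classes danger signs or severe malaria on D1 to D3 with parasitaemia as early treatment failure (ETF).
- Section 9.7.4 says that patients "classified as failures (within 14 days of treatment) will be treated with quinine", and that failures from D14 are handled as reinfections and given the allocated combination again.
- Section 9.7.1 bars antimalarials during the 42 days and says "Intake of these drugs leads to withdrawal of the patient from the ongoing active follow up". It does not exempt rescue treatment.
- Section 12.1.2 says that patients who stop treatment are followed under the study procedures to D42, and that the case report form is completed to D42 after quinine.

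**The concern.** A PP set should exclude children whose conduct of the trial departed from the plan, not children whose treatment failed. Here completion of the course and of the schedule is itself a condition of entry, and a failure can prevent both. Membership then depends on the outcome being estimated.

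The direction matters. If failures are removed at a similar rate in both arms, both success rates rise and the gap between them shrinks, so an inferior drug looks closer to the comparator. PP is analysed beside ITT in a non-inferiority trial as a check against dilution. A PP set that loses failures cannot do that job.

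**Working it through.** **Step 1. Which failures does the wording remove?** Dosing runs D0 to D2 and is supervised in the first attack (flow chart; sections 9.9 and 13.2.2).

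| Type of first-attack failure | Course completed? | Assessments completed? | PP status |
|---|---|---|---|
| Danger signs on D1 or D2 with parasitaemia (ETF) | No, drug stopped (12.1.1) | To D42 under 12.1.2 | Out, by definition |
| ETF on the D3 criteria, or late failure before D14 | Yes | 9.7.1 withdraws from active follow-up; 12.1.2 continues to D42 where treatment was discontinued and after quinine | Not determinable |
| Failure from D14 | Yes | 9.7.4 starts a new course; status of remaining first-attack visits not stated | Not determinable |

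Section 9.7.4 also mentions follow-up to D42, but that sentence follows the description of non-response to quinine and may cover only that case.

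**Step 2. Planning inputs (section 14.2).** The margin "has been chosen at 5" percentage points; one-sided alpha 5%; power 80%; Coartem success 97% (failure 2.7%); 174 per arm; 200 per arm enrolled to allow for 15% withdrawal. The plan's figure is approximately reproduced by the Farrington-Manning formula with 97.3% success in both arms. The restricted success rates under the null are 0.9334 and 0.9834:

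n = [1.645·√(0.9334·0.0666 + 0.9834·0.0166) + 0.842·√(2·0.973·0.027)]² / 0.05² = 171 per arm, within 3% of 174.

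At 97.0% the same formula gives 183. The sample size is not in dispute here; the step only anchors the test and the numbers.

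**Step 3. Effect on the PP rates.** Let s be the true success rate and f the share of failures that PP removes, assumed equal in both arms. The PP success rate is s / [s + (1 − s)(1 − f)]. With true rates exactly at the margin, 92% v 97%, and f = 25%:

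- Coarsucam: 0.92 / (0.92 + 0.08·0.75) = 0.92 / 0.98 = 93.88%
- Coartem: 0.97 / (0.97 + 0.03·0.75) = 0.97 / 0.9925 = 97.73%
- Difference −3.86 points instead of −5.00.

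**Step 4. Chance of declaring non-inferiority in PP.** Exact binomial enumeration, 170 per arm (200 × 0.85), one-sided 5%, margin 5 points:

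| f (assumed) | PP rates | Difference (points) | Farrington-Manning | Wald limit |
|---|---|---|---|---|
| 0% | 92.00 v 97.00 | −5.00 | about 5% | about 6% |
| 10% | 92.74 v 97.29 | −4.55 | 7% | 9% |
| 25% | 93.88 v 97.73 | −3.86 | 12% | 16% |
| 50% | 95.83 v 98.48 | −2.64 | 30% | 40% |
| 75% | 97.87 v 99.23 | −1.36 | 71% | 82% |

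Starting instead from 174 per arm and letting the set shrink as failures leave, the Wald limit gives 6.0%, 8.9%, 16.1%, 39.0% and 83.7%. The choice of test moves the figures by up to about ten points; the pattern is the same.

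Farther from the margin the effect is smaller. At 89% v 97% (174 per arm, Wald) the chance is 0.4% with failures kept, 2.2% at f = 25% and 13% at f = 50%.

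**The case against.** The strongest reply has four parts.

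*ITT keeps every one of these failures.* This stands. If success on both sets were required, the false-positive rate of the overall conclusion could not exceed that of ITT. The protocol does not state that requirement, however, and even under it PP would add little as a check.

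*Most failures finish the course, and rescue is itself directed by the protocol.* This largely stands. D3-criterion early failures and all late failures arise after the last dose. A reader might infer that every rescued failure drops out, because section 9.7.1 withdraws any child given an antimalarial. Section 12.1.2 points the other way for children on quinine, so the documents do not establish it. Nor does any passage say that a failure from D14 has incomplete first-attack assessments.

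*Deviations are graded at a blind review, and the wording is limited to major violations.* This stands against reading the rule as excluding any child who misses one visit or blood draw: nothing calls that a major violation, and section 13.2.4 expects missed visits. It does not rescue the danger-sign case. Section 14.4.3 lets the review grade deviations; it does not say the review may waive completion of treatment. Stopping drug may follow the protocol, but it is not completion.

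*The analysis plan will settle it.* Evaluability detail often belongs there. Here the protocol states the PP rule itself, and section 14.1 makes section 14 the basis of that plan.

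A reader might also infer that the PP test is close to self-fulfilling. That would need about three quarters or more of failures to be removed, and the text does not fix the share.

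**Conclusion.** The point holds in limited form. As written, PP loses failures whose dosing is stopped for danger signs, and its treatment of rescued failures and failures from D14 cannot be determined until the follow-up passages are reconciled. The resulting bias favours non-inferiority in one of the two primary sets.

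If the loss is confined to a small share of failures (10% to 25%), the false non-inferiority rate in PP at the margin is about 7% to 12% by Farrington-Manning (9% to 16% by Wald), against about 5% (6%) with failures kept. At half of failures it is about 30% (40%).

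These figures assume true rates of 92% v 97%, about 170 children per arm and the same share removed in each arm. They describe PP taken alone, not the trial's conclusion over both sets. The share removed appears nowhere in the protocol. The defect and its usual direction are established; its size is not.

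**What to change.** In section 14.4.1, and correspondingly in the analysis plan:

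1. State that any ITT child classed as ETF, late clinical failure or late parasitological failure, with no major deviation before that outcome, stays in PP as a failure, whether or not study drug was stopped, rescue or re-treatment was given, or later visits were missed.
2. Tie the required assessments to the endpoint: for the D28 PP set, those needed to classify the D28 outcome. Define a matching D42 set for the D42 analyses.
3. Reconcile sections 9.7.1, 9.7.4 and 12.1.2 on whether and how first-attack follow-up continues after rescue or re-treatment. Which clinical rule applies is for the sponsor and the investigator; the PP definition only needs one consistent statement.

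The cost is wording. No new data, visits or children are needed. The change should be made before database lock and without sight of results by arm.

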### Safety population

Safety population: all randomized patients who have got at least one dose of treatment, including patients with double vomiting or rejection at the first intake.

Number of patients in each population will be displayed by treatment group.

### Disposition of patients

The status of protocol deviations (minor/major) will be listed and discussed during a blind review meeting with the study committee.

## Statistical methods

All statistical analyses will be performed on SAS software (version 8.2 for PC).

All statistical tests will be performed at a 5% significance level and will be bilateral except for the non-inferiority analysis (unilateral confidence interval).

Distributions of parameters will be summarized by mean, standard deviation, median, minimum and maximum. These distributions will be compared using the Student t-test if normal distribution hypothesis is confirmed. Otherwise, distributions will be compared using the non-parametric Wilcoxon test.

All qualitative parameters will be summarized in contingency tables displaying frequencies and corresponding percentages.

For these parameters, a chi-square test (replaced by Fisher exact test if the expected frequency in any one of the cells of the contingency table is < 5) will be performed.

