## Identification of adverse events

At each follow-up visit (days 1, 2, 3, 7, 14, 21, 28, and 42, and any unscheduled day), study clinicians will assess patients according to a standardized clinical record form. A severity grading scale, based on toxicity grading scales developed by the WHO and the National Institutes of Health, Division of Microbiology and Infectious Diseases, will be used to grade severity of all symptoms, physical exam findings, and laboratory results as mild, moderate, severe or life threatening (Appendices 2 and 3). Any new event, or an event present at baseline that is increasing in severity, will be considered an adverse event.

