#### Laboratory variables analysis

Biological parameters will be summarized by group of treatment and overall at each time of measurement.

All abnormal variables will be graded and each parameter will be counted by grade.

The number of patients with abnormal data will be compared by grade between each treatment group and over the 2 years of follow-up

Transition tables will be provided between D0, D7 and D28 in order to assess the evolution of these parameters classified as normal/abnormal and by grade according to the laboratory ranges.

Absolute and relative changes to the baseline will be computed for each parameter for each attack. The evolution between D0 and D7 and D0 and D28 will be analyzed for each attack

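### Laboratory grades are ordered, but the protocol's default between-arm test ignores the order; for a uniform shift to worse grades this costs roughly 15 to 23 points of power

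*Protocol*

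**What the plan says.** Protocol section 14.5 (Statistical methods) gives one rule for categorical data. "All qualitative parameters will be summarized in contingency tables displaying frequencies and corresponding percentages", and then: "For these parameters, a chi-square test (replaced by Fisher exact test if the expected frequency in any one of the cells" is under 5). Rank methods appear only for quantitative data that fail normality: "Otherwise, distributions will be compared using the non-parametric Wilcoxon test". Ordered categories have no rule of their own. The level is common to all tests except non-inferiority: "All statistical tests will be performed at a 5% significance level and will be bilateral".

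Section 14.5.4.2 (Laboratory variables analysis) says "All abnormal variables will be graded and each parameter will be counted by grade" and "The number of patients with abnormal data will be compared by grade between each treatment group and over the 2 years of follow-up". It names no test. The grades are those of Appendix 3, and section 11.4 describes them as grading "laboratory results as mild, moderate, severe or life threatening". With normal included, that makes five ordered categories for most parameters and four for platelets, which have no grade 1.

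The same section also plans transition tables by grade, and absolute and relative changes from baseline, with the D0 to D7 and D0 to D28 evolution analysed for each attack.

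**The concern.** Read together, the two sections send an ordered severity scale to a test that treats grades as interchangeable labels. The phrase about comparing by grade can be read in two ways, and each has a weakness.

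- **One arm-by-grade table.** Up to 4 degrees of freedom are spent on any difference in pattern, so the test is diluted against a general move towards worse grades.
- **A separate two-by-two test of each exact grade.** Grade 1 against everything else pools normal children with grades 2 to 4. A more toxic drug that pushes children from grade 1 to grade 2 can then show fewer grade 1 children. Up to four 5% tests are also run per parameter.

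Section 6.2 lists biological tolerability as a comparison for first attacks, for repeat attacks and, as the impact of repeated treatment, for the whole cohort. A weak test makes it easier to report no difference in grades, which is the unsafe direction for a safety question.

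**Working it through.** **Inputs from the protocol.** 200 children per arm (section 8.1); two-sided 5% (14.5); five ordered categories, or four for platelets (Appendix 3). The protocol states no power, grade distribution or effect for this comparison, so there is no figure to reproduce. Everything below on distributions and effects is assumed.

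**Step 1: dilution by degrees of freedom.** If a 1-df ordered test has power 1 − β, its noncentrality λ is about (1.96 + z at 1 − β)². At 80% power, λ = (1.96 + 0.8416)² = 7.85. If all of that λ goes into a chi-square test with 4 df (critical value 9.488), power is 59.5%, a loss of about 21 points.

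| Ordered test | 4 df | Loss, 4 df | Loss, 3 df | Loss, 2 df |
|---|---|---|---|---|
| 40% | 24% | 16 | 13 | 9 |
| 50% | 31% | 19 | 16 | 10 |
| 70% | 48% | 22 | 17 | 10 |
| 80% | 59% | 21 | 16 | 9 |
| 90% | 74% | 16 | 12 | 7 |
| 95% | 84% | 11 | 8 | 4 |

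**Step 2: simulation of the section 14.5 rule** (chi-square, or Fisher when an expected count is below 5) against a tie-corrected Wilcoxon test. There were 1,500 trials per scenario, 200 per arm, and a common odds ratio (OR) for a worse grade. Distributions are for the better arm, normal to grade 4.

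| Assumed distribution (%) | OR | Section 14.5 rule | Wilcoxon | Loss |
|---|---|---|---|---|
| 30/25/30/13/2 | 1.5 | 40.5% | 61.8% | 21.3 |
| same | 1.7 | 64.8% | 85.7% | 20.9 |
| same | 2.5 | 98.9% | 99.8% | 0.9 |
| 70/15/10/4/1 | 1.5 | 33.1% | 48.9% | 15.8 |
| same | 1.7 | 52.9% | 74.5% | 21.6 |
| 88/8/2.5/1/0.5 | 1.5 | 18.9% | 30.2% | 11.3 |
| same | 2.0 | 53.7% | 72.5% | 18.8 |
| 80/13/5/2 (four categories, platelet-like) | 1.5 | 27.9% | 41.6% | 13.7 |

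A separate set of simulations with 20%, 40% and 70% abnormal gave chi-square 23/36/40% against Wilcoxon 41/58/62% at OR 1.5 (losses 18, 22, 22). At OR 1.8 it gave 49/69/74% against 72/87/90% (losses 23, 18, 16).

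**Step 3: tests of each exact grade.** With equal drugs, the chance of at least one nominally significant grade per parameter is about 13 to 16%. On direction, under the first distribution above with OR 1.5, the expected share in grade 1 falls from 25% to 22.7% in the worse arm, while grades 3 and 4 together rise from 15% to 18% + 3% = 21%.

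**Step 4: a shift that is not uniform.** Suppose the excess is confined to grades 3 and 4 and drawn from grades 1 and 2: 50/25/19/5/1 against 50/24/12/11/3. The section 14.5 rule then has 72% power and Wilcoxon 9%. A two-by-two test of grade 3 or worse compares 5 + 1 = 6% with 11 + 3 = 14%. The null standard error is √(2 × 0.10 × 0.90 / 200) = 0.0300. The alternative standard error is √((0.06 × 0.94 + 0.14 × 0.86) / 200) = 0.0297. Power is Φ((0.08 − 1.96 × 0.0300) / 0.0297) = Φ(0.71), about 76%. In another assumed case of this kind, chi-square had 65%, Wilcoxon 46% and the grade 3 test 81%. For an excess moved only from normal to grade 1, the section 14.5 rule had 71% and Wilcoxon 55%.

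**The case against.** The strongest objection is that section 14.5.4.2 already analyses the laboratory values themselves as changes from baseline, which section 14.5 sends to a t-test or Wilcoxon test. Under an idealised model in which the grades are cut from one continuous value, a Wilcoxon test on that value had 65% power at OR 1.5 and 92% at OR 1.8, as good as or better than an ordered test on grades. This stands as a limit on scope. A reader might infer that the whole biological tolerability comparison is underpowered, and the protocol does not support that. The value analysis does not remove the point, though: it compares average changes and does not ask whether one arm has more children in the worse grades, and the haemoglobin and creatinine cut-offs differ by age.

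Second, the ordered test is not uniformly better, as step 4 shows, and severe grades matter here: section 11.8 makes neutrophils below 400/mm³, which is grades 3 and 4 of Appendix 3, an event of special interest. This also stands, and it is why an ordered test should not be adopted alone.

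Third, the test is inferred, since 14.5.4.2 names none and the statistical analysis plan is not shown. That plan may name an ordered test. Section 14.1, however, makes section 14 its basis, and the rule in 14.5 is written for all qualitative parameters, so the protocol does state a default.

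A reader might also extend the point to adverse event intensity. Section 14.5.4.1 plans only incidence tables there, and section 10.2.3 mentions a comparison without a method, so the documents do not fix an unordered test for it. The wrong-direction effect for grade 1 likewise needs care: it arises when abnormal values are common, and the full grade tables would show it.

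**Conclusion.** The point holds for the between-arm comparison of laboratory grades only. By default it falls to an unordered test, or to separate tests of exact grades, although the scale is ordered. For a uniform shift to worse grades with 200 children per arm and five categories, the loss is roughly 15 to 23 points when the ordered test has about 40 to 90% power. It is somewhat smaller with four categories, and small once power is very high or very low. For shifts confined to one part of the scale the ranking can reverse.

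All power figures rest on assumed grade distributions and odds ratios, and on one grade per child, so they describe the first attack. Section 10.2.3 uses the episode as the unit for repeated treatment, which changes the sample size and adds clustering. The comparison is secondary and has no power target, and the primary conclusion is untouched. This is a cheap improvement to the safety analysis.

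**What to change.** In sections 14.5 and 14.5.4.2:

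1. State that ordered categories are compared with an ordered method. For each laboratory parameter, use one between-arm test of grade (Wilcoxon or proportional odds), with a child effect when attacks are pooled. Keep chi-square or Fisher for unordered categories.
2. Prespecify and test grade 3 or worse against lower grades for each parameter.
3. Show cumulative counts (grade 1 or worse, 2 or worse, 3 or worse) by arm in place of tests of each exact grade.

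This takes a few sentences and no new data. The price is two tests per parameter. With both at 5% and no adjustment, the chance of at least one false positive is at most 5% + 5% = 10% per parameter, against about 13 to 16% when every exact grade is tested. The grade 3 comparison must be tested and not only displayed, because the ordered test alone can miss an excess confined to the severe grades.
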